### Intervention and comparator {15}

We will adopt a structured approach to ensure both knowledge transfer and practical application, fostering sustained behaviour change for improved iron intake.Iron cookware distribution and cooking demonstration: Participants in the intervention group will receive standardized iron cookware for daily use. A set of iron cookware will include the following:Iron Kadhai (wok): A deep, round-bottomed cooking pan commonly used for stir-frying, sautéing, and deep-frying. This will be the primary vessel for preparing curries, vegetables, and other staple dishes.Iron Tava (griddle): A flat, circular pan traditionally made for chapatis, rotis, and dosas. Cooking flatbreads on an iron Tava will enhance dietary iron intake due to direct food contact with the surface.Iron Ganj (pot): A deep cooking pot used for boiling rice, lentils, and other staple foods. Prolonged cooking in iron pots has increased iron leaching into food, improving iron intake.Iron Sarata (ladle/spoon): A large, sturdy spoon for stirring and serving food. Frequent contact between the ladle and food during cooking may contribute to iron transfer.By providing a combination of these commonly used iron utensils, the intervention aims to increase dietary iron intake through routine meal preparation while being culturally and socially appropriate.To ensure effective and sustained adoption, they will be trained on:◦ Optimal cooking techniques—Emphasizing methods that enhance iron release, such as cooking acidic foods (e.g., tomato-based dishes).◦ Best practices and precautions—Guidance on dos and don’ts, including avoiding excessive scrubbing that may reduce the iron layer and ensuring consistent cookware usage.◦ Safe handling and maintenance—Instructions on proper care to extend the cookware’s lifespan and ensure safe cooking practices.

### Health education and behaviour change communication (BCC) sessions

The effectiveness of cooking with iron utensils will be evaluated alongside behaviour change communication (BCC) strategies, ensuring that participants adopt and sustain cooking practices that optimize iron absorption. To reinforce knowledge and promote long-term adherence, the study team will conduct group sessions and household visits, focusing on the role of dietary iron, i.e., understanding iron-rich food sources, factors that enhance absorption (e.g., vitamin C), and dietary inhibitors (e.g., tea, coffee, phytates); Anemia Prevention and Management which includes raising awareness about the consequences of iron deficiency and the importance of routine hemoglobin checks and Sustained Behaviour Change for encouraging the habitual use of iron cookware through community-driven approaches, including storytelling and role modelling by early adopters.

Participants in the intervention group will receive fortnightly group BCC sessions for the first 3 months, followed by monthly group sessions for the next 3 months (total, 9 group sessions over 6 months). In addition, monthly individual home visit sessions will be conducted throughout the 6-month intervention period to reinforce key messages, address practical barriers, monitor cookware usage, and offer personalized support. Each group session will last approximately 45–60 min, while home visits will be of 20–30 min duration, ensuring context-specific engagement and continuous motivation.

### Criteria for discontinuing or modifying the intervention {15b}

Participants who become pregnant during the trial will be withdrawn from the primary outcome analysis but may be followed up for safety outcomes with consent. Data collected up to pregnancy will be retained for analysis. Participants may discontinue at their own request or if advised by the study physician for medical reasons.

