### Concomitant care permitted/prohibited {15d}

Participants will be asked to avoid initiating iron supplementation or other medications that affect iron metabolism during the trial period, unless medically indicated. Any such use will be recorded, and participants will remain in ITT analyses.

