### Plans to promote participant retention and follow-up {25b}

Retention will be promoted through regular household visits, community meetings, and reminder phone calls/WhatsApp messages before scheduled assessments. Monthly home visits will reinforce adherence, troubleshoot problems, and monitor compliance. Compliance will be assessed by Food diaries maintained by participants; Unannounced spot checks by field staff, and Monthly supervisory visits. Compliance is defined as use of the provided iron cookware for ≥ 1 main meal per day on ≥ 4 days per week, sustained for ≥ 70% of the intervention period. Participants not meeting this criterion will be considered non-compliant for per-protocol analysis but will remain in the intention-to-treat (ITT) analysis. Outcome data (Hb, ferritin, and other biomarkers) will be collected for all randomized participants, even if they discontinue or deviate from the intervention, unless consent is withdrawn entirely.

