### Statistical methods {27}

#### Primary and secondary outcomes {27a}

Descriptive statistics will be used to summarize baseline characteristics. Continuous variables will be expressed as mean (SD) or median (IQR) as appropriate, and categorical variables as frequencies and percentages. Baseline differences between intervention and control groups will be assessed using independent *t*-tests (or Mann–Whitney *U* tests for non-normal data) and chi-square or Fisher’s exact tests for categorical variables. Standardized mean differences (SMDs) will be calculated, with an SMD < 0.1 indicating adequate baseline balance.

Continuous outcomes such as haemoglobin (Hb), serum ferritin, soluble transferrin receptor (sTfR), and transferrin saturation (TSAT) will be analyzed using linear mixed-effects models with fixed effects for group, time, and group × time interaction, and random effects for participants (and clusters if applicable). Binary outcomes such as anaemia prevalence, adherence, and adverse events will be analyzed using mixed-effects logistic regression. Risk ratios, odds ratios, mean differences, and 95% confidence intervals will be reported. The significance level will be set at *p* < 0.05 (two-tailed). Analyses will be performed using R software.

To provide a comprehensive evaluation of iron status, additional biomarkers will be assessed, including total iron-binding capacity (TIBC), erythrocyte protoporphyrin, mean corpuscular volume (MCV), and C-reactive protein (CRP). These indicators will enable differentiation between iron deficiency, anaemia of inflammation, and other causes of low Hb. Effect size (Cohen’s d) will be calculated for the primary outcomes (Hb and ferritin) to quantify the magnitude of intervention impact**.**

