### Analysis population {27b}

All randomized participants will be included in the analysis according to the group to which they were allocated (intention-to-treat, ITT). A per-protocol analysis will also be conducted for adherence-related outcomes, where compliance is defined as use of the provided iron cookware for ≥ 1 main meal per day on ≥ 4 days per week for at least 70% of the intervention period.

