### Missing data {27c}

Missing outcome data will be addressed using maximum likelihood estimation under the missing-at-random assumption. Multiple imputation with 20 datasets will be performed as a sensitivity analysis. Reasons for missingness (e.g., pregnancy, migration, withdrawal) will be documented. Additional sensitivity analyses will include complete-case analysis and per-protocol analysis to evaluate robustness of findings.

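### Section 15b withdraws women who become pregnant from the primary analysis while other rules keep them in, so the primary analysis set is not uniquely defined

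*Protocol article*

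**What the plan says.** Five places in the protocol article bear on a woman who becomes pregnant after randomisation.

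- Criteria for discontinuing or modifying the intervention (15b): "Participants who become pregnant during the trial will be withdrawn from the primary outcome analysis". She may be followed for safety with consent. The section then adds: "Data collected up to pregnancy will be retained for analysis". It does not name the analysis.
- Plans to promote participant retention and follow-up (25b): haemoglobin, ferritin and the other biomarkers "will be collected for all randomized participants, even if they discontinue or deviate from the intervention, unless consent is withdrawn entirely".
- Analysis population (27b): "All randomized participants will be included in the analysis according to the group to which they were allocated (intention-to-treat, ITT". No exception is made for pregnancy.
- Missing data (27c): "Missing outcome data will be addressed using maximum likelihood estimation under the missing-at-random assumption". The same section says: "Reasons for missingness (e.g., pregnancy, migration, withdrawal) will be documented".
- Sample size (19): pregnancy is counted within the anticipated 10% attrition.

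Two further passages give context. Section 27a analyses continuous outcomes with "linear mixed-effects models with fixed effects for group, time, and group × time interaction" and random effects for participants, a model that can use incomplete records. Section 15d covers another post-randomisation event that affects iron status, starting iron or related medication, and decides the other way: "Any such use will be recorded, and participants will remain in ITT analyses".

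**The concern.** Removing a woman from the primary analysis because of something that happened after randomisation means that the groups compared are no longer the groups randomised. If pregnancy is more frequent in one arm, or if the women who become pregnant differ in iron status in a way that varies by arm, the comparison can be biased.

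The more immediate problem is that the rules do not yield one dataset. A result labelled intention to treat could be produced with these women in, partly in, or out. If that choice is made once data are available, it can depend on the results.

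The uncertainty may also reach the field. Section 15b foresees only safety follow-up after pregnancy, while 25b foresees continued outcome collection. Samples not taken cannot be recovered later.

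**Working it through.** **1. What each rule does to one woman.** Take a woman who becomes pregnant in month 10, with the Table 1 visits for the primary outcome (baseline, 6 and 12 months).

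| Reading | Source | Values in the primary model |
|---|---|---|
| Full removal | 15b, withdrawal sentence taken literally | none |
| Censoring at pregnancy | 15b, retention sentence, with 27c | baseline, 6 months |
| All values as collected | 27b with 25b | baseline, 6 and 12 months |

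Each reading has support in the text, and only the first removes her from the randomised set. Section 25b governs collection rather than the analysis set, so it does not by itself contradict 15b. The direct conflict is between the withdrawal sentence of 15b and 27b, with 27c also pointing away from removal.

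**2. The plan's own sample size.** Inputs from section 19: SD 1.2 g/dL, difference 0.5 g/dL, two-sided 5%, power 80%, attrition 10%.

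n per arm = 2 × [1.2 × (1.960 + 0.842) / 0.5]² = 90.42.

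Dividing by 0.9 gives 100.47, so 101 per arm and 202 in total. The stated figure reproduces. (Rounding to 91 before dividing gives 102 per arm, 204 in total.) Power for haemoglobin is 84.2% with 101 per arm and 80.2% with 10% lost. Pregnancy is already inside that 10%, so the issue is bias and definition, not sample size.

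**3. How many women.** The documents give no pregnancy rate. Assuming 2%, 5% or 10% over follow-up, about 4, 10 or 20 of 202 women are affected (0.02, 0.05 and 0.10 × 202 = 4.04, 10.1 and 20.2).

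**4. Possible bias under full removal.** Let p₁ and p₀ be the proportions removed in the intervention and control arms. Let d be the difference in mean haemoglobin between removed and retained women, taken as equal in both arms. An arm's full mean is its retained mean plus p × d, so

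bias = −(p₁ − p₀) × d.

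All values of p and d below are assumptions. The signs reverse if d or the imbalance reverses.

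| p₁ v p₀ | Size of d (g/dL) | Size of bias (g/dL) | Share of 0.5 g/dL |
|---|---|---|---|
| 5% v 5% | any | 0 | 0% |
| 10% v 5% | 0.6 to 1.2 | 0.03 to 0.06 | 6% to 12% |
| 8/101 v 4/101 | 1.2 | 0.0475 | 9.5% |
| 8% v 2% | 0.6 to 1.2 | 0.036 to 0.072 | 7% to 14% |
| 10% v 0% (extreme) | 1.2 | 0.12 | 24% |

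For scale, the standard error of the difference with 91 per arm is 1.2 × √(2/91) = 0.18 g/dL. If d differs between arms, the formula becomes −(p₁d₁ − p₀d₀), which need not be zero at equal rates.

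**5. What cannot be computed.** Table 1 names CRP-adjusted ferritin as the primary outcome. The article gives no SD or target difference for it, so the figures above illustrate haemoglobin only.

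**The case against.** The best defence is that 15b, read whole, already means censoring at pregnancy. It retains earlier data, 27a fits a model that accepts partial records, 27c treats pregnancy as a reason for missingness, and section 19 counts it as attrition. That reading is coherent, and it is the rule recommended below. Leaving later values out is also defensible in itself, since the objective concerns non-pregnant, non-lactating women. What the defence cannot do is remove the withdrawal sentence, which says the opposite for the primary analysis, or show that the retained data are meant for that analysis rather than a secondary or safety one.

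Three stronger readings are tempting, and the documents do not support them.

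- A reader might infer that a woman pregnant in month 10 certainly loses her baseline and 6-month values. That is one reading only, because 15b goes on to retain data up to pregnancy.
- A reader might infer that pregnancies will be found more often in the intervention arm, which has monthly home visits as part of behaviour change communication. Those visits are specified for 6 months. Sections 15c, 25b and 29 and the harms section mention household visits or spot checks without naming an arm, and no ascertainment procedure differs by arm. Earlier detection alone would not change how many women are removed; only pregnancies never detected would.
- A reader might infer that the primary result will be biased. With equal rates and equal prognosis the bias is zero, and the larger values above rest on chosen imbalances and a full 1 SD difference.

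It is also fair to say that censoring does not abolish the bias: the 12-month comparison then rests on MAR after pregnancy.

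**Conclusion.** The point stands as a contradiction within the protocol that leaves the primary analysis set open. It rests on the text alone and needs no assumption about pregnancy rates. It is not a matter left to a later analysis plan, because the protocol states the rules and they disagree.

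Bias is a possibility of unknown direction and size. On assumed rates, with d between 0.6 and 1.2 g/dL, the haemoglobin bias runs from 0 to about 0.05–0.07 g/dL (10% to 14% of the target difference). It reaches 0.12 g/dL (24%) only if 10% are removed from one arm and none from the other. These figures are modest beside a standard error of 0.18 g/dL and do not carry over to ferritin. The case for correction is that the analysis set should be fixed in advance.

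**What to change.** Replace the withdrawal sentence in 15b with a statement to this effect: women who become pregnant remain in the intention-to-treat primary analysis set; their baseline and all pre-pregnancy values enter the mixed model; values after pregnancy are treated as missing under MAR in the primary model; a sensitivity analysis uses all outcome values collected under 25b; and the number of pregnancies is reported by arm. Name the primary analysis explicitly in the sentence on retained data, and add a cross-reference in 27b and 27c.

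Sections 15b and 25b should also be reconciled on whether outcome data are collected after pregnancy. That is for the investigators to settle; the analysis rule above works either way, but the sensitivity analysis is informative only if such values exist.

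The cost is a short text change and one extra sensitivity analysis, with no change to the sample size. The remaining weakness is that the primary model still relies on MAR after pregnancy, which the sensitivity analysis probes but does not remove. The change is best made before enrolment, and in any case before outcome data are seen.

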### Strategies to improve adherence and monitoring {15c}

Adherence will be promoted and monitored through like monthly household visits by field staff to provide reinforcement, troubleshoot issues, and encourage compliance. Food diaries maintained by the participants documented meals prepared using iron cookware. Spot checks during unannounced household visits to observe real-time usage. Structured surveys and interviews to explore barriers and facilitators. Compliance will be defined as use of the provided iron cookware for at least one main meal/day on ≥ 4 days per week, maintained for ≥ 70% of the intervention period. This threshold is based on prior iron-cookware RCTs. Focus group discussions (FGDs) to further refine adherence strategies and address community concerns. Adherence outcomes will be reported, and both per-protocol and intention-to-treat analyses will be performed.

### Concomitant care permitted/prohibited {15d}

Participants will be asked to avoid initiating iron supplementation or other medications that affect iron metabolism during the trial period, unless medically indicated. Any such use will be recorded, and participants will remain in ITT analyses.

### Outcomes {16}

The outcome measures and assessment time points are summarized in Table 1. Blood samples will be collected at each time point for the biochemical analysis of iron status markers. Dietary intake and adherence to cookware use will be monitored using structured questionnaires and periodic household visits.

**Table 1 Tab1:** Summary of primary, secondary, and exploratory outcomes with measurement variables, analysis metrics, aggregation methods, and time points (baseline to 12 months)

Outcome type	Measurement variable	Analysis metric	Method of aggregation	Time points
Primary outcome	Serum ferritin (µg/L), CRP-adjusted	Mean change from baseline	Mean ± SD, mean difference (95% CI)	Baseline, 6 months, 12 months
Secondary outcomes	Haemoglobin (g/dL)	Mean change from baseline	Mean difference (95% CI)	Baseline, 6 months, 12 months
	Soluble transferrin receptor (mg/L)	Mean change from baseline	Mean difference (95% CI)	Baseline, 6 months, 12 months
	Transferrin saturation (%)	Mean change from baseline	Mean difference (95% CI)	Baseline, 6 months, 12 months
	Anaemia prevalence (Hb < 12 g/dL, WHO)	Proportion with anaemia	Risk difference, risk ratio (95% CI)	Baseline, 6 months, 12 months
	Nutrition knowledge and practice score	Change in score	Mean difference	Baseline, 6 months, 12 months
	Adherence to iron cookware use (≥ 1 main meal/day, ≥ 4 days/week)	Proportion adherent	Percentage adherence	Monthly monitoring; summarised at 6 months, 12 months
	Adverse events (GI symptoms, iron overload, other harms)	Proportion with ≥ 1 adverse event	Frequency counts, percentages	Ongoing; summarised at 3, 6, and 12 months
Exploratory outcomes	Cost-effectiveness (per unit Hb and ferritin increase)	Incremental cost-effectiveness ratio (ICER)	ICER	6 months, 12 months
	Dietary modifiers (vitamin C intake, tea/coffee, phytates)	Effect modification	Subgroup analyses	Baseline, 6 months, 12 months
	Subgroup analysis by baseline anaemia	Effect difference	Interaction tests	6 months, 12 months
	Community-level adoption of cookware post-trial	Proportion of households continuing usage	Adoption rate (%)	Endline at 12 months; post-trial sustainability follow-up

### Harms {17}

Harms included any adverse event (AE) temporally associated with trial participation/intervention, whether or not considered related, and serious adverse events (SAEs) (death, life-threatening event, inpatient hospitalization/prolongation, significant disability, or important medical events The expected AEs for this trial include minor gastrointestinal symptoms (e.g., nausea, constipation, abdominal discomfort, and dark stools); skin/contact events (e.g., minor burns while cooking); and laboratory abnormalities consistent with changes in iron status. Potential though unlikely safety signals of excess iron will be monitored using ferritin and transferrin saturation (TSAT). The participant timeline, including schedule of enrollment, interventions, and assessments, is shown in Table 2.

**Table 2 Tab2:**
[figure not shown]
Participant timeline: schedule of enrollment, interventions, and assessments [17]^a^

^a^ Recommended content can be displayed using various schematic formats

^b^ List target timepoints and acceptable time windows in this row (e.g., 30 ± 3 days)

^c^ Arrow indicates continuous delivery of intervention (e.g., Use of iron pots & BCC)

#### Ascertainment and frequency

Harms will be assessed systematically at every study contact (baseline, 3, 6, and 12 months) and during monthly home visits in the intervention period, using a structured checklist and open-ended queries. Participants may also self-report harms at any time via a study phone number/WhatsApp. Field workers will document onset, duration, severity, actions taken, and outcome; supervisors verify within 48 h.

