### Data collection methods {25}

#### Plans for assessment and collection of outcomes {25a}

Data collection will include both quantitative and qualitative measures to evaluate iron status, dietary intake, adherence, and perceptions of the intervention. Quantitative data will be obtained through structured questionnaires to capture sociodemographic characteristics, health history, and dietary practices, as well as a 24-h dietary recall and Food Frequency Questionnaire (FFQ) to estimate dietary iron intake and food patterns. Laboratory investigations will be carried out at an NABL-accredited laboratory, where trained phlebotomists will collect blood samples for analysis of hemoglobin (Hb), serum ferritin, serum iron, soluble transferrin receptor (sTfR), transferrin saturation (TSAT), total iron binding capacity (TIBC), C-reactive protein (CRP), erythrocyte protoporphyrin, and mean corpuscular volume (MCV). These parameters will be measured at baseline, 6 months, and 12 months, with Hb and ferritin additionally assessed at 3 months. Duplicate testing will be performed on 10% of samples to ensure validity. Qualitative data will be collected through semi-structured interviews and focus group discussions (FGDs) to explore perceptions, facilitators, and barriers to cookware adoption and BCC acceptability, supplemented by field observations recorded during household visits to triangulate adherence and contextual factors. All assessors and laboratory staff will be trained and blinded to group allocation, and standard operating procedures (SOPs) will be followed at all stages to ensure consistency and data quality.

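### As written, harms are actively elicited at monthly home visits described only for the iron-cookware arm, so the between-arm comparison of women with at least one adverse event is tilted against the intervention

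*Protocol article*

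**What the plan says.** Under Harms {17}, Ascertainment and frequency, the protocol article states: "Harms will be assessed systematically at every study contact (baseline, 3, 6, and 12 months) and during monthly home visits in the intervention period". Elicitation is active, "using a structured checklist and open-ended queries". Of the recording it says: "Field workers will document onset, duration, severity, actions taken, and outcome". Participants in either arm may also report harms themselves at any time by phone or message.

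The home visits are scheduled in the section on health education and BCC sessions. The paragraph opens: "Participants in the intervention group will receive fortnightly group BCC sessions for the first 3 months". It continues: "In addition, monthly individual home visit sessions will be conducted throughout the 6-month intervention period to reinforce key messages". The sections on adherence {15c} and retention {25b} describe monthly visits in terms of encouraging and checking compliance, and compliance is defined by use of the iron cookware. Under Trial design {12} controls receive standard care and keep their usual utensils.

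Table 1 lists adverse events as a secondary outcome, measured as the proportion of women with one or more events and summarised at 3, 6 and 12 months by counts and percentages. Section {27a} then says: "Binary outcomes such as anaemia prevalence, adherence, and adverse events will be analyzed using mixed-effects logistic regression". Nothing limits that analysis to contacts made in both arms.

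On blinding, {24a} says that participants and the field investigators who deliver the intervention cannot be blinded. Section {25a} says: "All assessors and laboratory staff will be trained and blinded to group allocation".

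**The concern.** The expected events are mostly mild and easily forgotten: nausea, constipation, abdominal discomfort, dark stools, small burns. Whether such an event enters the record depends on how often someone asks. If one arm is asked monthly for six months and the other only at 3, 6 and 12 months, the arms can differ in recorded events when their true risks are equal.

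The error has one direction. It makes iron cookware look less well tolerated than it is. That matters for a low-cost strategy which the Discussion hopes to see taken into public programmes, where tolerability is part of the case. The staff asking at home visits are also delivering the intervention and know the arm, so the blinding sentence in {25a} cannot hold for these harms.

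**Working it through.** **Arm sizes.** Section {19} gives SD 1.2 g/dL, difference 0.5 g/dL, 80% power and two-sided 5%. Then n = 2 × (1.96 + 0.842)² × 1.2² / 0.5² = 90.4, so 91 per arm. Multiplying by 1.1 for attrition gives 100.1, so 101 per arm and 202 in total, as stated. These figures supply only the arm sizes used below. The document gives no adverse event rate.

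**Elicitation contacts after baseline, as written.**
- Control: months 3, 6 and 12, so 3.
- Iron arm: months 1 to 6 and month 12, so 7 distinct time points. If home visits are separate from the 3- and 6-month assessments, 6 + 3 = 9.

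**Model A, no recall beyond the contact.** Assume the same chance q of a recorded event at every contact in both arms. P(at least one) = 1 − (1 − q)^k, with k = 7 against 3. The last column is the chance of a significant difference at two-sided 5% when comparing two proportions with 101 women per arm.

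| q (assumed) | Iron, k = 7 | Control, k = 3 | Risk ratio | Chance of false significance |
|---|---|---|---|---|
| 0.02 | 13.2% | 5.9% | 2.24 | 42% |
| 0.05 | 30.2% | 14.3% | 2.12 | 78% |
| 0.10 | 52.2% | 27.1% | 1.93 | 96% |

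**Model B, partial recall.** Assume events occur at the same monthly rate λ in both arms, the last month before a contact is fully recalled, and earlier events are recalled with probability r.
- Control intervals are 3, 3 and 6 months: expected recorded events = λ(3 + 9r).
- Iron arm has six one-month intervals, then one of 6 months: λ(7 + 5r).
- P(at least one) = 1 − exp(−expected events).

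| λ (assumed) | r (assumed) | Iron | Control | Risk ratio | Chance of false significance |
|---|---|---|---|---|---|
| 0.05 | 0.25 | 33.8% | 23.1% | 1.46 | 39% |
| 0.05 | 0.50 | 37.8% | 31.3% | 1.21 | 16% |
| 0.05 | 0.75 | 41.6% | 38.6% | 1.08 | 6% |
| 0.10 | 0.25 | 56.2% | 40.8% | 1.38 | 59% |
| 0.10 | 0.50 | 61.3% | 52.8% | 1.16 | 23% |
| 0.10 | 0.75 | 65.9% | 62.3% | 1.06 | 8% |

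The difference in expected recorded events is λ(7 + 5r) − λ(3 + 9r) = 4λ(1 − r). It is positive for every r below 1 and zero only at r = 1, where both arms have 12λ.

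**Blinding.** Under {24a} those who deliver the intervention know the arm. The home visits are part of the intervention, and field workers record harms at them. The statement in {25a} that all assessors are blinded therefore cannot cover harms.

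**The case against.** A reader might infer that the protocol denies controls any monthly visit. It does not say so. The harms sentence names a period and not an arm. Section {25b} plans household visits for retention, and Trial monitoring {29} plans monthly household spot checks, both without naming an arm. The schedule in Table 2 is not available in the text reviewed and might settle it. This stands, and it is why the point is confined to what is described. Still, neither of those passages links its visits to a harms checklist for controls.

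The between-arm comparison is also less firmly planned than it may look. Table 1 gives only counts and percentages for adverse events, whereas the anaemia row has a risk difference and risk ratio. The model sentence in {27a} also lists adherence to iron cookware, which has no control counterpart. That weakens the inference but does not remove it: adverse events are named for regression, and even percentages shown side by side carry the same imbalance.

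It would be tempting to say that recorded harms will double, or reach a ratio of 2.8. That top value needs 9 separate contacts, a 2% chance per contact and no recall: 1 − 0.98⁹ = 16.6% against 5.9%. The documents do not support choosing that case over a modest one.

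Self-report is open to both arms and partly offsets the imbalance, though it is passive. Laboratory abnormalities, also counted as expected events, are found at fixed blood draws and do not depend on how often women are asked.

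A reader might also infer that safety review will be misled. The listings are described as blinded and reviewed by a monitor only if the ethics committee requires one, with no between-arm test. Extra contacts can only help to detect harm in the individual woman.

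**Conclusion.** The concern holds for the plan as written: active harms contacts are described at about 7 post-baseline time points in the iron arm (possibly 9) and 3 in control, and the proportion with at least one event is then listed for regression without adjustment for this. The direction is against the intervention unless recall is perfect.

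The size cannot be derived from the documents. Under the assumed rates the spurious risk ratio is about 1.1 to 1.5 with partial recall and 1.9 to 2.2 with none, at 7 against 3 contacts. The conclusion rests on the inference that controls have no equivalent monthly harms contact. If they do, the bias goes and what remains is a gap in the description. The outcome is secondary and the primary laboratory outcome is not touched.

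**What to change.** - Base the between-arm adverse event comparison on events elicited at the 3-, 6- and 12-month contacts made in both arms, plus serious adverse events from any source.
- At those contacts use the same checklist and the same recall period in both arms, and ask about the whole interval again whatever was reported earlier. Without this, events already reported at a home visit could drop out of the iron arm's count.
- Record the source of each report on the adverse event form (scheduled contact, home visit, self-report). Present home-visit events separately and descriptively. No safety surveillance is lost.
- If controls are in fact visited monthly with the same harms checklist, state that instead; the restriction is then unnecessary.
- Limit the blinding statement in {25a} to laboratory outcomes, in line with {24a}.

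The cost is wording and one field on a form, best settled before recruitment, which the Trial status section dates to December 2025. Fewer events enter the formal comparison. Some imbalance may remain, because women asked monthly may remember events better at the shared contacts; the report should say so.
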